## Discussion

Recurrent depression is highly prevalent and reducing risk of relapse is of particular importance in those who are likely to become suicidal when depressed. This trial will be the first to evaluate the efficacy of Mindfulness-based Cognitive Therapy (MBCT) for this population, and the first to use a design that compares MBCT with both an active 'control' treatment and usual care. This trial will provide the opportunity to investigate further treatment approaches known to be promising and to learn more about mechanisms of treatment in order to refine this approach. The use of a 'dismantling design' for this purpose is unusual.

We selected the 'control' treatment from several options. One was to compare the MBCT 'package' with an alternative group-based package, for example group-based CBT that would entail comparable group attendance and homework assignments. There are two reasons why we rejected this option. First, treatments like CBT were designed to treat acute depression rather than prevent relapse, and appear to be less effective in preventing relapse [11]). Secondly, whatever the outcome of such a comparison, we could not answer our key scientific question: which component of relapse-prevention treatment is critical to success?

In a 'dismantling' paradigm, the comparison treatment is identical to the index treatment, but has a critical component removed. Given that the most complex aspect of MBCT is intensive training in meditation, we decided that the control treatment should follow the same group format as MBCT but *without *any training in meditation. Thus participants have the same number and length of sessions as MBCT, controlling for group and therapist support, but with short lecture-type presentations and group discussions instead of meditation training. These cover the psycho-educational components of learning about depression, links between thoughts and feelings, and how to self-monitor these for signs of impending recurrence. We have developed a rigorous manual for this treatment package and piloted it in both Oxford and Bangor. Note that a dismantling design does not match treatments for homework assignments since meditation needs more homework. If MBCT is more effective than CPE, then it will be for further research to address the question whether homework would have enhanced efficacy.

The intention in this trial is to examine MBCT for people with severe recurrent depression, including suicidal ideation or behaviour. We considered including only participants who at the outset acknowledge experience of suicide ideation or behaviour. However the stigma associated with suicidality and the frequent failure to disclose suicidal thoughts and behaviours to clinical staff, made us suspicious that this would reduce recruitment to the trial. For example consultation with GP practices revealed reluctance to circulate information about a trial explicitly targeting suicidal depression to patients whose practice notes might not record such a history. We were also concerned that people would be less likely to refer themselves to the trial if posters and other material focused on suicidal ideation or behaviour. Although the stigma surrounding suicidal ideation and behaviour is unfortunate and should be challenged, recruitment is crucial in trials. So, although the special interest in suicidal depression is shared with referring clinicians, recruitment is open to all who have experienced recurrent depression, rather than specifying minimum levels of suicidality as an inclusion criterion. We then stratify participants according to history of suicidality reported on standardised measures used in the initial assessments of eligibility, and use these measures as covariates in the definitive analysis. We still expect most participants to report some history of suicide ideation or behaviour, even though this is not explicit in recruitment materials.

We encourage all participants to continue their 'treatment as usual' as determined through consultations with their GP and other mental health professionals, for the duration of the study. In addition we ask those not allocated to MBCT not to take up a regular meditation practice over the year of follow-up, and thus to restrict their choice of treatment. As we cannot enforce this in practice, we ask at each assessment whether participants have taken up any treatment or meditation practices so that we can take this into account in analysis. Furthermore we shall offer all participants, especially those receiving TAU alone, treatment classes of their choice after the end of the study. The research team will maintain contact with those in the TAU group throughout the trial, and encourage them to make full use of the services available to them. As participants may relapse to suicidal depression during the study, we explain the limits of confidentiality and the procedure for dealing with severe suicidal ideation to all participants before asking them to give consent.

In summary, recurrent depression is common and gives rise to increased risk of morbidity and mortality for those who become suicidal when depressed. There is an urgent need: first to develop treatments that can address the needs of this group and produce sustainable reductions in risk of recurrence; and, second to identify the critical therapeutic factors in order to refine the approach for the future. This trial will address both objectives.

## Appendix 1: Statistical Analysis Plan

The primary outcome measure will be the time to relapse or recurrence meeting DSM-IV criteria for a major depressive episode (American Psychiatric Association, 1994) on the Structured Clinical Interview for DSM-IV (SCID, Spitzer et al., 1992). Occurrence of relapse or recurrence will be assessed after treatment (T1), and at three (T2), six (T3), nine (T4) and twelve (T5) months thereafter by trained psychologists blind to participants' treatment condition. If the interview establishes that symptoms meeting diagnostic criteria for major depression have been present since the last assessment, we shall ask participants when this episode of depression started (and ended, if they are no longer symptomatic). 'Return to treatment' will also be treated as a relapse or recurrence if, in the judgment of a blind rater, the participant experienced exacerbation of their symptoms that would have met the criteria for Major Depression in the absence of immediate treatment.

The analysis will be by 'intention to treat' (ITT). The time (in weeks) of relapse or recurrence to Major Depression, as defined above, will be the dependent variable in survival analysis. The treatment group and stratification variables will be used as predictors.

For participants who are lost from the trial we shall use their available measures and then censor them at the time of their last observation. Since only a participant's first relapse or recurrence to Major Depression will contribute to the survival analysis, the subsequent loss of that participant will not affect the analysis.

Participants who miss one or more follow-up assessments, but are then assessed at a later time point will be asked whether they have experienced a relapse or recurrence according to SCID diagnostic criteria since the last assessment, including time periods which would have been covered in missed assessments. This will enable us to assess the time to relapse and thus to censoring.

We shall use the clinician-rated Hamilton Rating Scale for Depression (HRSD, to assess severity of depression at all time points. We shall follow De Rubeis et al. (2005) and Hollon et al (2005) in using a score of 14 or more on the HRSD to indicate relapse, thus complementing the SCID diagnosis. HRSD scores also provide a quantitative measure of outcome that strengthens the dichotomised outcome of diagnosis, because, as a quasi-continuous measure, it has more power to detect differences between groups.

The other quantitative measures used at baseline, before treatment, and at times T1 to T5 are the Beck Depression Inventory (BDI-II), Beck Hopelessness Scale (BHS), Beck Scale for Suicide Ideation (BSS current) and the EQ5D. We shall calculate the 'area under the curve' (AUC) of each measure to give a single score. For the EQ5D this is known as a QALY.

Missing items within individual outcome measures will be treated according to the instructions for that measure. If two or more observations for quantitative measures are available between T1 and T5, then we shall use linear regression to estimate the missing values and the AUC. If there is only one observation available between T1 and T5 then we shall estimate the remaining values from the general slope estimated from all participants with two or more observations. If no observations for T1 to T5 are available then the AUC is also missing. If the trend among participants with full data departs from linear, then we shall use the observed trend to estimate the missing values.

For the quantitative measures we shall use a mixed-model analysis of covariance (AnCova). We shall use baseline measures as covariates, and multi-level modeling to take account of the clustering of participants within classes within centres. As covariates we shall also use the stratification variables and treatment group, together with the number of sessions attended and, in the MBCT group, number of hours of home practice. These will allow us to estimate how the response to the two treatments depends on their 'dose'.

Potential moderators to be examined include gender, residual symptoms of depression (e.g. HRSD score and BDI-II score at baseline) and stability of remission, course of previous history (chronic vs episodic), and age of onset.

Recurrence of suicidal ideation, both within episodes of major depression and over the follow-up period, is an important secondary outcome. Initially we shall examine recurrence of suicidality specifically for those participants who relapse to Major Depression and had a history of suicidal ideation or behaviour at entry to the trial. Then we shall compare severity of suicidal symptoms, as measured by the Beck Scale for Suicide Ideation (BSS current) and the MINI suicide-tracking measure, across the follow-up period for all participants, whether or not they relapsed or became suicidal. Finally we shall compare suicidal cognitions (and ability to let go of cognitions that occur), at baseline, T1 and T5 only between groups using AnCova, with T0 as covariate and T1 and T5 as separate outcomes.

By assessing cognitive measures relevant to risk of relapse to depression, namely mindfulness, suppression, self-compassion, rumination, self guides, autobiographical memory and executive capacity, before and immediately after treatment and at the end of follow-up, we can use them in an explanatory analysis to study factors that mediate efficacy. We shall use regression analysis (binary logistic regression for the dichotomous outcome of relapse and linear regression for the worst HRSD score during follow-up) to explore whether the change from T0 to T1 in each of these measures can account for the effects of treatment on risk of relapse.

Where necessary we shall transform variables closer to Normal distributions for AnCova. Where data are missing, we shall use data from alternative sources, notably therapists on the trial and referring general practitioners. We shall also use sensitivity analysis to assess the effect of including participants whose data on relapse is collected by these means.

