### Inclusion criteria

Principal inclusion criteria for the study are:

1) Age between 18 and 70 years, because depression in old age is related to different factors than depression in earlier stages of life [13,14].

2) Meeting enhanced DSM-IV criteria for a history of Recurrent Major Depression, namely a history of at least three episodes of depression, of which two must have occurred within the last five years, and one within the last two years [15]. Although previous suicidality is recorded in detail, thus facilitating stratification, prior experience of suicidality is not a prerequisite for participating in the trial.

3) Meeting the NIMH guidelines for recovery or remission at the time of baseline assessment. Potential trial participants are deemed *not *to be in recovery or remission, and hence *ineligible*, if they report at least one week during the previous 8 during which they experienced *either *a core symptom of depression (depressed mood, anhedonia) *or *suicidal feelings and at least one other symptom of depression, which together are not attributable to bereavement, substances or medical condition, but are impairing functioning.

4) Giving informed consent.

5) Consent received from the participant's General Practitioner.

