### Assessment of Eligibility and Baseline Measures

Before the first assessment session, researchers explain the trial to participants and give them the information sheet again. After they have had opportunity to discuss any questions, the researchers seek written informed consent after telling participants that they have the right to withdraw from the research at any time.

We ask consenting participants to provide information about their socio-demographic background and assess their eligibility in more detail using semi-structured clinical interviews and self-completed questionnaires. The researchers assess current and past diagnostic status using the Structured Clinical Interview for DSM IV (SCID [16]), the Suicide Attempt Self Injury Interview (SASII [17]) and the Hamilton Rating Scale for Depression (HRSD[18]). They ask participants to complete a crisis card, and to describe past and current treatments for depression and past meditation and yoga experience.

They then ask participants themselves to complete the Beck Scale for Suicide Ideation (BSS-current [19] and worst [20]), the Mini International Neuropsychiatric Interview (MINI) Suicidality Tracking measure [21], the Beck Depression Inventory (BDI-II [22]) to assess severity of current symptoms of depression, the Beck Hopelessness Scale (BHS [23]) to measure current levels of hopelessness, a questionnaire assessing occurrence of life events [24], a measure of global functioning (Clinical Outcome Routine Evaluation, CORE [25]), a measure of general quality of life (Euro-QOL EQ-5D [26]), a questionnaire assessing history of trauma (Childhood Trauma Questionnaire, CTQ [27]), and two short measures of anxiety and depression symptoms (GAD7 [28] and Patient Health Questionnaire, 9-item version, PHQ9 [29]). If participants meet all inclusion and none of the exclusion criteria for the study, they enter the study and are invited to the second pre-treatment assessment session.

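### The HRSD relapse rule (14 or more) has no matching limit at entry, so an unchanged entry score can be counted as a relapse in this complementary outcome

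*Protocol article*

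**What the plan says.** The primary outcome rests on the SCID. Appendix 1 states: "The primary outcome measure will be the time to relapse or recurrence meeting DSM-IV criteria for a major depressive episode". A return to treatment also counts, if a blind rater judges that symptoms had worsened enough.

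Appendix 1 then brings in the clinician-rated HRSD, used "to assess severity of depression at all time points". Following two cited studies, it adopts a cut-off as a further relapse indicator: "using a score of 14 or more on the HRSD to indicate relapse, thus complementing the SCID diagnosis". The HRSD also serves as a quasi-continuous outcome, and its baseline value is a potential moderator, under "residual symptoms of depression (e.g. HRSD score and BDI-II score at baseline) and stability of remission".

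Entry is governed by inclusion criterion 3: "Meeting the NIMH guidelines for recovery or remission at the time of baseline assessment". A candidate fails it if, in at least one of the previous 8 weeks, a core symptom or suicidal feelings occurred with at least one other symptom, "which together are not attributable to bereavement, substances or medical condition, but are impairing functioning". The section on eligibility and baseline measures lists the HRSD among the instruments of the first assessment session. Neither the inclusion nor the exclusion criteria attach a limit to it.

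**The concern.** Remission at entry and HRSD relapse in follow-up are measured on different yardsticks. Criterion 3 asks about the kind of symptom, its cause and its effect on functioning; the HRSD rule asks only for a total score. A person whose symptoms do not impair functioning, are put down to bereavement, substances or a medical condition, or include neither a core symptom nor suicidal feelings passes criterion 3 whatever the HRSD total.

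The other two routes to relapse refer to onset or worsening: the SCID interview asks when the episode began, and return to treatment requires an exacerbation. The HRSD rule, as written, requires no change. Someone who scores 15 at T0 and 15 at T1 meets it at T1.

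That participant has persistent symptoms, not a relapse. Counting such cases adds events that do not represent a failure of prevention. It also makes HRSD and SCID relapse disagree for a reason that lies in entry status, which weakens the complementary role Appendix 1 gives the HRSD rule. Using baseline HRSD as a covariate does not change how these cases are coded.

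**Working it through.** **Step 1: can both rules hold for one person on one day?**

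| | Entry remission (criterion 3) | HRSD relapse (Appendix 1) |
|---|---|---|
| Measure | Core symptom or suicidal feelings, plus another symptom | Total HRSD score |
| Impairment required | Yes | No |
| Other causes set aside | Bereavement, substances, medical condition | None stated |
| Window | Any week of the previous 8 | Score at the assessment |
| Reference to baseline | Not applicable | None stated |

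No line of either rule excludes the other. Remission under criterion 3 with an HRSD of 14 or more is possible, and nothing in the HRSD rule removes such a person from the count later.

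**Step 2: how much could it matter?**

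Inputs from the Sample Size section: relapse of 39% (MBCT) and 57% (CPE), 120 per arm, 5% level, stated power 80%. Two-sided testing is assumed.

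Reproducing the plan's figure with the normal approximation for two proportions:

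power = Φ{[d√n − 1.96√(2p̄(1 − p̄))] / √(p₁(1 − p₁) + p₂(1 − p₂))}

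With d = 0.18, n = 120 and p̄ = 0.48 this gives Φ{[1.972 − 1.385] / 0.695} = 80.1%, in agreement with the plan. This figure is not in dispute; it only anchors the illustration.

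Assumptions for the illustration, none of them in the documents:
- a share q of each arm enters at 14 or more and stays there;
- the remaining participants follow the planning rates, which were set for recurrence and are borrowed here for the HRSD rule.

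The observed rate is then q + (1 − q)p, and the difference is (1 − q) × 18 points.

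| q | MBCT | CPE | Difference (points) | Participants affected per 120 | Power, all 120 per arm | Power, only those below 14 at T0 |
|---|---|---|---|---|---|---|
| 0 | 39.0% | 57.0% | 18.0 | 0 | 80.1% | 80.1% |
| 2% | 40.2% | 57.9% | 17.6 | 2.4 | 78.4% | 79.3% |
| 5% | 42.1% | 59.2% | 17.1 | 6 | 75.8% | 78.0% (114 per arm) |
| 10% | 45.1% | 61.3% | 16.2 | 12 | 71.3% | 75.8% (108 per arm) |
| 15% | 48.2% | 63.5% | 15.3 | 18 | 66.7% | 73.3% (102 per arm) |

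For example, at q = 10%: 0.10 + 0.90 × 0.39 = 0.451 and 0.10 + 0.90 × 0.57 = 0.613, a difference of 0.162.

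The last column applies the same formula with n = 120(1 − q) and the rates 39% and 57%. Under these assumptions the restriction costs less power than the dilution does. The power columns show relative cost only, since the trial was not sized for HRSD-defined relapse.

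**The case against.** Four arguments stand against making much of this.

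First, the HRSD rule is one sentence, without a model, risk set or event time, and it is adopted by following two cited studies whose own conditions cannot be seen. In a population entered in remission, the word relapse already suggests a return of symptoms. This stands in part: the article nowhere says that an unchanged score is to be counted. But Appendix 1 is headed as the statistical analysis plan and the main text refers to it for detail, so its rule has to be read as written, and as written it admits the case.

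Second, criterion 3 is strict. One qualifying week in 8 is enough to exclude, so entry at 14 or more needs an unusual symptom picture. This stands. A reader might infer from the moderator list that the plan expects many such entrants; it shows only that residual symptoms are expected, not scores at or above 14.

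Third, the illustration borrows rates from another outcome, invents the share, and assumes that nobody above the threshold improves. This also stands. Some may remit or respond to treatment, in which case the dilution is smaller.

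Fourth, the plan commits to intention to treat, and the proposed subset leaves out randomised participants and narrows the population of this analysis. The subset is defined by a score taken before randomisation, so the comparison remains randomised. An all-randomised sensitivity analysis meets the rest of the point.

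**Conclusion.** The gap is real but minor. The HRSD relapse rule, as Appendix 1 states it, can score an unchanged entry score as a relapse, because nothing at entry or in the rule prevents it.

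Three stronger readings are tempting, and the documents support none of them:
- **That the primary result is compromised.** It is not: the survival analysis uses SCID relapse and blind-rated return to treatment, and the HRSD threshold plays no part in it.
- **That the arms are compared unfairly.** Randomisation balances high entry scores in expectation, so what remains is dilution and misclassification.
- **That the trial loses a known amount of power.** The share at or above 14 at entry is not given, and no power was claimed for this indicator.

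On the assumed shares of 5% to 10%, with full persistence and the borrowed rates, an 18-point difference becomes about 17 to 16 points. The continuous HRSD analysis, which adjusts for baseline, does not depend on the threshold.

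**What to change.** Add to Appendix 1 that:
- HRSD-defined relapse is analysed among participants with an HRSD below 14 at T0;
- the number at or above 14 at T0 is reported for each arm;
- the same analysis in all randomised participants is given as a sensitivity analysis;
- every participant stays in the SCID primary analysis and in the continuous HRSD analysis.

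The cost is a few lines of text. The HRSD is already collected at the eligibility session, so no new data are needed. The downside is that a few participants leave this one complementary analysis, which then speaks for those below the threshold at entry. Counting a relapse only after a score below 14 has been recorded is another possible rule, but it would depend on scores taken after randomisation; the T0 restriction does not.

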## Methods/Design

This is a multi-centre, randomised controlled trial. We randomise participants between Mindfulness-Based Cognitive Therapy (MBCT) in addition to Treatment As Usual (TAU), Cognitive Psycho-Education (CPE) in addition to TAU, and TAU alone. In doing so, we stratify participants by (a) research centre (Oxford or Bangor) (b) cohort (c) history of suicidality (none, ideation or suicidal attempt) and (d) whether or not they were taking antidepressants in the 7 days before their first assessment. We originally proposed to stratify by centre, cohort, suicidal behaviour (ideation versus attempt), number of previous episodes of depression (3 or 4 versus 5 or more), and brooding (high versus low scores on a subscale of the Ruminative Response Style questionnaire). However we later changed these, with ethical approval, to reflect the inclusion of participants taking antidepressants or without suicidal ideation. We undertake randomisation by e-mail to the remote randomisation centre at the North Wales Organisation for Randomised Trials in Health (NWORTH) at Bangor University. The randomisation algorithm uses dynamic allocation to protect against subversion while ensuring that each arm of the trial is comparable with respect to the stratification variables. For validation the randomisation e-mail also includes additional information including the participant's date of birth, gender and date of assessment.

We monitor treatment effects over a period of one year. Assessments by trained assessors who are blind to treatment allocation (and whose blindness is checked within each assessment session) take place directly before and after the start of the treatment (T0 and T1), and at three (T2), six (T3), nine (T4) and twelve months (T5) after T1 (see Figure 1 for details of participant flow through the trial). We also offer treatment 'reunions' to participants in both MBCT and CPE at both 6-8 weeks and 6 months after treatment.

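### Missing follow-up scores for the secondary AUC outcomes each get one unbounded predicted value, which can be impossible and can lose precision against a repeated-measures model

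*Protocol article*

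**What the plan says.** Appendix 1 of the protocol article reduces each quantitative measure to one number: "We shall calculate the 'area under the curve' (AUC) of each measure to give a single score". Visits are at T1 and then "three (T2), six (T3), nine (T4) and twelve months (T5) after T1" (Methods/Design). The rule for missing visits has four parts:

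- **Two or more of T1–T5 observed:** "we shall use linear regression to estimate the missing values and the AUC".
- **One observed:** "estimate the remaining values from the general slope estimated from all participants with two or more observations".
- **None observed:** "If no observations for T1 to T5 are available then the AUC is also missing".
- **Curvature:** "If the trend among participants with full data departs from linear, then we shall use the observed trend to estimate the missing values".

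The resulting AUC enters a mixed-model AnCova. The Appendix gives no limit to the scale range, no arm-specific slope and no allowance for the uncertainty of the filled values. Its one sensitivity analysis concerns relapse data obtained from therapists or general practitioners, not these scores.

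**The concern.** The rule is deterministic single imputation by extrapolation, with a line that may rest on two points three months apart. Participants enter in remission and may then relapse, so a straight line through two early visits is a fragile guide to the remaining nine months. Three things are at stake:

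- values that the scale cannot take;
- loss of precision in outcomes that the Appendix includes partly because a quasi-continuous score has more power;
- for participants seen once, a later course that is the same in every arm by construction.

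The rule governs the AUCs of the quantitative measures, including the QALY.

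**Working it through.** **Inputs from the document.** Visits at 0, 3, 6, 9 and 12 months (Methods/Design). 5% significance level, 375 recruited 2:2:1 (so 150 per active arm), 20% attrition, 12 groups of 10 per active arm, ICC 0.05, detectable MBCT–CPE difference 0.45 SD at 80% power (Sample Size).

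**Assumptions not in the document.** Exchangeable correlation ρ between visits of 0.4 to 0.8, or AR(1); equal variance at each visit; dropout at random and monotone. For the share of impossible values, an underlying mean of 10 and SD of 10 on a 0–63 scale.

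**1. The plan's own figure.** Design effect 1 + 9 × 0.05 = 1.45; effective n = 120/1.45 = 82.8 per arm. The normal approximation gives a detectable 0.436 SD, or 82.5% power at 0.45. A t reference on 22 df gives 79.0%. The stated 0.45 SD is reproduced.

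**2. Impossible scores.** A line through T1 and T2 gives T3 = 2·T2 − T1, T4 = 3·T2 − 2·T1 and T5 = 4·T2 − 3·T1. For HRSD 14 then 6, the five values are 14, 6, −2, −10, −18. The 12-month trapezoid mean is (7 + 6 − 2 − 10 − 9)/4 = −2. For EQ-5D 0.60 then 0.85, T5 = 1.60 and the mean is 2 × 0.85 − 0.60 = 1.10, more than one QALY in a year. In simulation on the 0–63 scale, 28–47% of such T5 values fell outside the range.

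**3. Precision.** The trapezoid mean has weights (0.125, 0.25, 0.25, 0.25, 0.125), with sum of squares 0.21875. A T1–T2 participant has weights (−1, 2), with sum of squares 5. The weights sum to 1 in both cases, so the variance is ρ + (1 − ρ) × sum of squares.

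At ρ = 0.6:
- full data: 0.6 + 0.4 × 0.21875 = 0.6875
- T1–T2 only: 0.6 + 0.4 × 5 = 2.6, ratio 3.78
- 20% lost after T2, plan's rule: 0.8 + 0.2 × 3.78 = 1.56
- dropping them: 1/0.8 = 1.25
- likelihood model: regressing the mean on T1 and T2 leaves coefficients 0.359 and 0.484, explained variance 0.5727 and residual 0.1148, so (0.5727 + 0.1148/0.8)/0.6875 = 1.04

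The same calculation for other patterns (variance relative to full data):

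| Loss pattern | Correlation | Plan's rule | Drop | Likelihood |
|---|---|---|---|---|
| 20% after T2 | 0.4 | 2.08 | 1.25 | 1.07 |
| 20% after T2 | 0.6 | 1.56 | 1.25 | 1.04 |
| 20% after T2 | 0.8 | 1.23 | 1.25 | 1.02 |
| 20% after T2 | AR(1) 0.8 | 1.28 | 1.25 | 1.05 |
| 5% after each of T1–T4 | 0.4 | 1.35 | 1.25 | 1.06 |
| 5% after each of T1–T4 | 0.6 | 1.18 | 1.25 | 1.04 |
| 20% after T3 | 0.6 | 1.07 | 1.25 | 1.02 |
| 20% after T1 | 0.6 | 1.09 | 1.25 | 1.10 |

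With a lost fraction f, filling in is worse than dropping only if the variance ratio of a filled participant exceeds (2 − f)/(1 − f), which is 2.25 at f = 0.2. A T1–T2 participant has 6.4 at ρ = 0.4, 3.78 at 0.6 and 2.13 at 0.8.

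Power at 0.45 SD with 150 per arm, the 1.45 design effect, 20% lost after T2 and ρ = 0.6 is 74% under the plan's rule, 82.5% dropping cases and 89% with the likelihood model.

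**4. Dilution.** A common slope cancels between arms, so one-visit participants contribute only the difference present at T1. If a share p has only T1, the expected contrast is (1 − p) × AUC effect + p × T1 effect. With no effect at T1 that later grows, the shrinkage is p: 5% at p = 0.05 and 20% at p = 0.20 (simulated −3.61 against −4.53). With a constant effect there is none (−4.48 against −4.49). The personal line does not dilute.

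**The case against.** Several points on the other side stand.

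- **Dropping cases.** A reader might infer that the rule is always worse than discarding incomplete participants. It is not. That holds mainly for loss after T2 at low or moderate correlation. At exchangeable 0.8 the rule is marginally better (1.23 against 1.25), for loss after T1 or T3 it is better, and for spread losses it can go either way.
- **Within-person error.** The ratio 5/0.21875, about 23, is tempting to quote, but it leaves out between-person variance. On total variance the ratio for a T1–T2 participant is 2.1 to 6.4.
- **Standard errors.** One might infer that treating filled values as data makes the standard error falsely small. Simulation under random dropout showed no gross understatement; for example, the mean model SE was 0.921 against an empirical SD of 0.904 for 20% lost after T2 with a constant effect.
- **Returners.** The Withdrawal section asks those who leave treatment to keep attending, and the Appendix foresees missed visits followed by a return. There the line interpolates: with T1 and T5 seen, the sum of squares is 0.5, not 5.
- **Reading of the text.** That the regression is per person is an inference from the contrast with the general slope in the next sentence. The curvature clause can change the shape of the fill, but it adds neither a range limit nor arm-specific slopes.
- **Other HRSD summaries.** HRSD is also used as a cut-off of 14 and as a worst score, so the AUC is not its only summary.

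None of this removes the missing bound, the pooled slope, or the loss against a likelihood model in most of the patterns examined.

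**Conclusion.** The concern holds in a limited form. The rule can produce impossible scores; given the personal-line reading, that is arithmetic and needs no distributional assumption. It can cost precision against a likelihood repeated-measures model: 1.56 against 1.04 for 20% lost after T2 and 1.18 against 1.04 for spread losses at ρ = 0.6, with no gain if all losses follow T1 (1.09 against 1.10). Dilution is confined to one-visit participants in arms whose courses diverge, and is at most about their share of the sample.

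The sizes rest on assumed correlations and dropout patterns, since the document gives only the total of 20% attrition and not when it occurs. A reader might infer that the trial's main conclusion is at risk. It is not: the primary outcome is time to relapse, analysed by survival methods with censoring, and does not use these values. The change should be made, but it is not critical.

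**What to change.** Replace the fill-in rule in Appendix 1 with a mixed model for repeated measures on the observed T1–T5 scores. Include arm by visit, baseline by visit, the stratification variables, and a class random effect in MBCT and CPE. Estimate the AUC difference between arms as a contrast of the visit means with weights 0.5, 1, 1, 1, 0.5 times 3 months.

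Where an individual AUC is needed, use multiple imputation by arm, restricted to the scale range. This applies to the QALY and to the suicide-ideation AUC in the mediation work described under Analysis.

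The AUC estimand is unchanged. The cost is new wording and modest extra programming.
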